**Methods:**

This noninterventional, multicenter, 3-month prospective study will recruit patients from 4 medical clinics and 2 endocrinology or diabetes clinics. Patients will be identified using appointment lists and enrolled through consecutive sampling during routinely scheduled consultations. To be eligible, patients must be aged ≥18 years, diagnosed with T2DM, and treated with insulin. Utility and productivity will be measured using the EQ-5D-5L questionnaire and Institute for Medical Technology Assessment Productivity Cost Questionnaire, respectively. Questionnaires will be completed 4, 8, and 12 weeks after recruitment. Generalized estimating equation models will be used to investigate productivity losses and utility decrements associated with incident hypoglycemic events while controlling for individual patient characteristics. A total of 500 patients will be enrolled to ensure the precision of HEOR estimates.

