### Study Population

In Canadian clinical practice, patients with T2DM who are on insulin can be followed up by a family physician or a specialist [18]. Therefore, patients will be recruited from 4 medical clinics and 2 endocrinology or diabetes clinics. To increase generalizability, patients will be recruited from the 2 largest Canadian provinces, Ontario and Quebec. Patients will be identified using appointment lists and enrolled through consecutive sampling during routinely scheduled consultations. To be eligible, patients must be aged ≥18 years, diagnosed with T2DM, and treated with insulin. There are no restrictions on insulin regimens (eg, short-acting, long-acting, or mixed insulin). Given the lack of reimbursement, the use of insulin pumps is limited in the treatment of T2DM [19]. Patients must also be able to understand and read English or French and provide informed consent. Patients will be excluded if they participate in a clinical trial. A screening log will be used to document the participation rates.

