#### Independent Impact of Hypoglycemia

Generalized estimating equation (GEE) models will be used to investigate productivity losses and utility decrements associated with incident hypoglycemic events while controlling for individual patient characteristics. For utility, two separate models will be presented: one for the EQ-5D index and one for the visual analogue scale. For productivity losses, one main analysis will be presented for the total number, and separate models for each module will be presented as a complementary analysis. The potential model-confounding covariates are presented in Table S1 in Multimedia Appendix 1. Independent variables were identified based on existing literature and previous work from the Alliance for Canadian Health Outcomes Research in Diabetes [34]. Diabetes complications (micro- and macrovascular) to be included in the models are those preconized by HTA agencies for CUAs in T2DM [4,6,7]. On the basis of the current reference study for hypoglycemic utility values [5], the number of hypoglycemic episodes will be log-transformed to facilitate model fitting. The original scale will be tested using sensitivity analyses. Moreover, transformations of continuous independent variables will also be tested in the sensitivity analyses (Table S1 in Multimedia Appendix 1). The presence of multicollinearity will be tested, where important collinearity will be defined as a variance inflation factor of >10. Owing to the short duration of the study, all covariates, except hypoglycemia, will be considered time invariant for model simplicity. If vascular complications occur during the study period (incident cases), a history of macrovascular and microvascular complications will be treated as a time-varying covariate. The main models will not include interaction terms, as large-scale studies evaluating the impact of diabetes complications on utility have not demonstrated any interaction between vascular events and event history and among the different vascular events [35-37]. A sensitivity analysis will be performed to test for the interaction between hypoglycemic events and determinants, namely, a history of hypoglycemia and diabetes complications.

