
Confounding is a concern in observational research [28]. Before implementing this study, independent variables were thoroughly identified, and each known variable will be measured to limit confounding. To reflect real-world practice, independent variables that will be extracted from patients’ medical files will represent the last available value, which may not reflect the current unknown value. Moreover, some independent variables will be self-reported, potentially leading to residual confounding. Nevertheless, there are no unmeasured known confounders, and the potential impact of an unmeasured unknown confounder will be tested using *E* values [52,53]. There is evidence that a cross-sectional design may overestimate the impact of T2DM complications on utility because of the underlying heterogeneity across patients [37]. Therefore, a longitudinal design with time-varying exposure will help protect against time-invariant confounding (natural heterogeneity) [40,46-48]. A GEE model will be used to account for the correlation associated with repeated measures from the same individual. Although mixed models provide a flexible framework compared with the GEE model, they require a large sample size and may be computationally demanding. Therefore, the simpler GEE method will be used to deal with this noncomplex data set (no large-scale data analysis, single level of clustering, and absence of nonstochastic time-varying covariates, eg, time from baseline). In addition, it is acknowledged that a GEE model is comparable with a random intercept model for continuous outcomes. A drawback of the GEE model is the assumption that the data are MCAR [40,46-48]. Therefore, if the data are not MCAR, the WGEE will be used to ensure the robustness of the estimates [50]. Furthermore, reminders and incentives should help to minimize the rate of missing data.

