Patients will be recruited from several regions throughout Quebec and Ontario, Canada, to increase the external validity of the results. However, recruitment sites will be limited to urban areas and may not be representative of rural areas. The real-world design and broad eligibility criteria will ensure that the HEOR estimates are generalizable to a target population for future reimbursement purposes. It is assumed that recruitment through clinical sites only will not affect the representativeness of the sample as patients with diabetes have regular follow-ups with their health care providers, thereby capturing most eligible patients and not only patients in worse condition. Furthermore, enrolling patients from both medical and diabetes clinics will be representative of the target population. Although probability sampling is the gold standard for ensuring sample representativeness, it is often not feasible in Canada because many jurisdictions lack electronic patient databases, particularly family practice. Yet, systematic participant recruitment as consecutive sampling using appointment lists also helps minimize selection bias (including oversampling). Participation rates will be recorded to document the risk of selection bias. It should be noted that the COVID-19 pandemic may affect patient productivity and utility. However, given the use of the GEE model to estimate the independent impact of hypoglycemia on the HEOR estimates, the results are expected to be valid and generalizable.

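### The main GEE models have no visit or within-patient calendar-time term, and the plan relies on the GEE itself to deal with COVID-19

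*Protocol article*

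**What the plan says.** The outcome schedule is fixed: "Questionnaires will be completed 4, 8, and 12 weeks after recruitment". The patient reports the number of events in the last 28 days at the same three time points (Assessments and Study Calendar).

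Under Independent Impact of Hypoglycemia, the main models are GEEs in which "all covariates, except hypoglycemia, will be considered time invariant for model simplicity". The one exception is a vascular complication that occurs during follow-up. The event count is log-transformed, and the original scale is a sensitivity analysis. On the covariate list: "The potential model-confounding covariates are presented in Table S1 in Multimedia Appendix 1". That appendix is not shown.

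Under Strengths and Limitations, the GEE is preferred to a mixed model because the data set is described as having "no large-scale data analysis, single level of clustering, and absence of nonstochastic time-varying covariates, eg, time from baseline". The clustering meant is the patient: "A GEE model will be used to account for the correlation associated with repeated measures from the same individual".

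The same section says: "It should be noted that the COVID-19 pandemic may affect patient productivity and utility". It then expects valid and generalizable results "given the use of the GEE model to estimate the independent impact of hypoglycemia on the HEOR estimates".

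On sites, Study Population says that "patients will be recruited from 4 medical clinics and 2 endocrinology or diabetes clinics", in two provinces.

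**The concern.** Weeks 4, 8 and 12 are a nonstochastic time-varying covariate. Leaving visit out of the mean model is a choice, and the text presents it as a property of the data. The plan considers an autoregressive working correlation, so it recognizes the order of the visits for the correlation but not for the mean.

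The COVID-19 statement does not follow. The working correlation affects efficiency and how within- and between-patient information is weighted. It does not remove a calendar trend from the mean. E-values (Unmeasured Confounding) are meant for an unknown confounder, whereas the pandemic is named. The Discussion's claim that no known confounder goes unmeasured fits badly with that.

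Reported events may fall over 12 weeks as recording tires, and utility or productivity may shift with learning, season or pandemic wave. If both happen, the event coefficient takes up part of the shared movement. The estimates are meant as inputs to cost-utility models, and the article reports that cost-effectiveness ratios reacted strongly to changes in these decrements. The decrements it cites for nonsevere events are about 0.003 to 0.008, so a drift of 0.02 exceeds the effect of a single event.

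**Working it through.** **Inputs from the article.** Three visits; 6 clinics; 17% three-month incidence of severe events; 400 evaluable and 500 enrolled patients. The sample size reproduces: 68 / 0.17 = 400, and 400 / (1 - 0.20) = 500. That gives about 400 x 3 = 1,200 observations.

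**Is a time term excluded or merely not mentioned?** The Methods make hypoglycemia the only time-varying regressor apart from incident complications. The Discussion gives time from baseline as its example of what is absent. A visit term, or calendar time that changes within a patient, would contradict both passages. It is therefore not a detail left to the covariate table.

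**Size.** The article gives no trend figures, so these are assumptions. No closed form applies, so linear GEEs were simulated.

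*Check 1.* 400 patients x 3 visits, SD 0.2, within-patient correlation 0.7. Reported nonsevere events fall 30% from week 4 to week 12 and utility drifts up by 0.02 to 0.03.
- Original scale, true value -0.005 per event: estimates -0.0062 to -0.0070. Ratios 0.0062 / 0.005 = 1.24 and 0.0070 / 0.005 = 1.40, so 24-40% too large. The shift of 0.0012 to 0.0020 is below one standard error (0.0028). Visit indicators restore -0.005 with the same standard error.
- Planned log(1 + events) scale, true value -0.020, about 2 events per 28 days: estimates -0.023 to -0.025. Ratios 1.15 and 1.25, so 15-25% too large.
- A separate exchangeable-GEE simulation with 400 x 3 and the same trends gave 17-22% (log scale) and 27-36% (original scale).
- Fall in events with no utility drift: -0.0050, no bias.

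*Check 2.* Exchangeable GEE with robust standard errors, 500 x 3, log scale, true value -0.020, between-patient SD 0.13, within-patient SD 0.12, 400 replicates per scenario, no patient covariates.

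| Assumed trend per visit | No visit term: bias (95% CI coverage) | Visit term added: bias |
|---|---|---|
| None | 0% (0.96) | 0% |
| Utility +0.02 only | -2% (0.97) | -3% |
| Utility +0.01, log event rate -0.2 | +15% (0.92) | -1% |
| Utility +0.02, log event rate -0.4 | +56% (0.55) | -1% |

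Over two intervals the third row is a fall of 1 - exp(-0.4) = 33% with a drift of 0.02, close to Check 1. The fourth is 1 - exp(-0.8) = 55% with 0.04, an extreme case. Monte Carlo error is about 0.0065 / sqrt(400) = 0.0003, or 1.6% of 0.020, so biases of 2-3% are noise. The standard error was 0.0062-0.0067 without the visit term and 0.0066-0.0067 with it.

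**Clinic.** Suppose one third of patients are specialist patients with a 25% incidence of severe events against 13% (overall 0.25/3 + 2 x 0.13/3 = 0.17) and utility 0.05 lower. The specialist share is (0.25/3)/0.17 = 0.49 among patients with an event and (0.75/3)/0.83 = 0.30 among the others. The cross-sectional bias is 0.19 x 0.05, about 0.0094. A true -0.060 becomes -0.069 under independence but -0.0615 under exchangeable, a bias of 0.0015 / 0.060 = 2.5%, or about a tenth of a standard error (0.016). In the Check 2 setting, clinic SDs of 0.03 in utility and 0.3 in log event rate gave -3% when uncorrelated, +18% at correlation -0.7 and +26% at -1.

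**The case against.** The covariate table is not shown. A reader might infer that the models have no clinic or enrolment-date term at all. The documents do not support this: clinic, clinic type, province or enrolment date could be listed there as time-invariant covariates, and the Methods exclude only time-varying ones. A reader might also infer that naming one level of clustering is an error with six clinics. It describes the correlation structure, and it stays correct if clinic enters as a fixed effect. Both objections stand.

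The trends are assumed, and bias needs both of them. It would be too strong to say that shared trends are attributed to hypoglycemia. They can be, if event counts and the outcome both move. This also stands.

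There are partial safeguards. Diary counts replace questionnaire counts when higher, reminders are sent, and each patient is followed for only 12 weeks, which limits calendar drift within a patient. They make the assumed trends less likely or smaller. They do not remove them, since a diary can also tire.

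On clinic, the models control for patient characteristics that probably explain much of the difference between specialist and primary-care patients, such as hypoglycemia history, HbA1c and complications. The simulations adjusted for none of these. The plan falls back on an exchangeable structure when results are similar across structures, and there the bias in the severe-event example is small. The 18-26% figures need strongly correlated clinic effects and no patient covariates.

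None of this answers the exclusion of visit or the reasoning on COVID-19.

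**Conclusion.** The concern holds for time. The article excludes a visit term and within-patient calendar time from the main models, on the ground that no such covariate exists, although the study calendar supplies one. Its statement that the GEE makes the results valid despite the pandemic is unsupported unless pandemic timing enters the model.

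The consequence is conditional. With a 30% fall in reported events and a utility drift of 0.02 to 0.03, the coefficient is about 15-25% too large on the planned log scale and 24-40% on the original scale. There is no material bias if only one of the two trends. The direction follows the assumed signs: events falling while utility rises inflates the decrement, and both falling would shrink it. Productivity was not simulated, but the same logic applies. The enrolment period is not stated, so the size of a pandemic effect cannot be judged.

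For clinic, absence of a term is not established and the expected bias under an exchangeable structure is small. It is a point to confirm.

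**What to change.** 1. Add visit (week 4, 8, 12) as a categorical covariate to every main model for utility and productivity: 2 degrees of freedom.
2. Add the calendar period of questionnaire completion, for example by quarter. If enrolment turns out to be short, check that this is not nearly collinear with visit.
3. Under Strengths and Limitations, remove the claim that time from baseline is absent as a reason for the GEE. A GEE takes a time covariate without difficulty, so the choice of method need not change.
4. In the same section, replace the COVID-19 sentence with a statement of this adjustment.
5. Confirm that Table S1 includes clinic or clinic type. If not, add clinic as a fixed effect (5 degrees of freedom). Six clinics are too few for robust standard errors clustered by clinic. The remark on a single level of clustering can then stay.

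The cost is about 7 to 10 degrees of freedom out of roughly 1,200 observations, with no extra patients or questionnaires. The visit terms left the standard error essentially unchanged. The date of completion must be kept for each questionnaire, which the article does not state.

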### Conclusions

Robust evidence on the productivity and utility of insulin-induced hypoglycemia is lacking in Canada. Currently, available data on productivity loss have not been estimated using a validated questionnaire, thereby increasing the risk of bias [3,8,9]. A systematic review published in 2021 identified 42 unique instruments for measuring productivity, and the authors recommended the iPCQ for use in economic evaluations [60]. As for the current evidence on utility decrement due to hypoglycemia, Canadian data are limited to vignette studies (ie, bespoke descriptions of impaired health states), which are not the preferred source of utility owing to their inherent drawbacks [10-12]. This study will generate high-quality HEOR estimates for future economic modeling of T2DM.

## Appendix

Multimedia Appendix 1 Potential independent variables for the generalized estimating equations models.

## Abbreviations

ADA: American Diabetes Association
CADTH: Canadian Agency for Drugs and Technologies in Health
CUA: cost-utility analysis
GEE: generalized estimating equation
HAT: hypoglycemia assessment tool
HEOR: health economics and outcomes research
HTA: health technology assessment
iMTA: institute for Medical Technology Assessment
iPCQ: institute for Medical Technology Assessment Productivity Cost Questionnaire
MCAR: missing completely at random
NICE: National Institute for Health and Care Excellence
NSHE: nonsevere hypoglycemic event
QIC: quasi-likelihood under the independence model criterion
SAQ: self-assessment questionnaire
SHE: severe hypoglycemic event
T2DM: type 2 diabetes mellitus
TTO: time trade-off
WGEE: weighted generalized estimating equation
